#### Mediator training (Module 1)

2.2.1.

The intervention starts with the acquisition of future transcultural mediators from different migrant communities (e.g., Turkish community) at the project sites in Berlin and Hamburg. Contact and acquisition is through the EMC network, and considers the social environment of the migrants. Potential mediators are recruited, for example, in religious, social, and migrant self-organizations, cultural centers or in educational institutions using flyers, posters, or by word of mouth. The recruitment targets individuals with advanced German skills and extended networks in the respective migrant community. The mediators are provided with knowledge about the general and health situation of migrant families in Germany, and about the German health care system, in extensive training courses (Module 1), with a special focus on medical rehabilitation, its goals, contents and possible uses. The mediators are also taught didactic and methodological skills in the training sessions, which enable them to pass on their acquired knowledge to other members of the migrant communities as multipliers in independently organized information events. The entire training comprises 48 teaching units of 45 min each, which are distributed over nine training days. The sessions are led by instructors with subject-specific experience (e.g., pediatricians on the topic of chronic diseases in children). Participants receive a training folder with prepared information on the training content. On the last day of training, the trained mediators give a presentation in small groups on one of the topics covered in the training (e.g., requesting on medical rehabilitation for children and adolescents) as a final exam. A total of at least 120 mediators (60 in Berlin and 60 in Hamburg) will thus be trained in three years from 2020 to 2022.

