	Questionnaire 1 for mediators (at each individual appointment)	Dose received	Subjective evaluation of the implementation of the training date
			Recommendations of the mediators to improve training
	Questionnaire 2 for mediators (after completion)	Recruitment/reach	Sociodemographic data of the mediators
		Dose delivered	Data on attendance at the individual training dates
		Dose received	Subjective evaluation of the implementation of the entire training
			Recommendations of the mediators to improve training
Information events in the native language (Module 2)			
	Documentation sheet for mediators	Recruitment/reach	Number of participants
		Fidelity	Implementation of the module in comparison to the conceptual design (e.g., duration, contents); Feedback from mediators on implementation problems with closed and open-ended questions
		Dose delivered	Location of the information session
			Duration of the information session
			Information session language
			Sociodemographic data on the mediator performing the mediation
			Materials used
			Information on topics covered
			Subjective evaluation of implementation of the information session from the mediator’s point of view
	Questionnaire for participants in twelve languages	Recruitment/reach	Sociodemographic data of the participants
		Dose received	Subjective evaluation of implementation of the information session
Individual support for rehabilitation requests (Module 3)			
	Monitoring of the implementation	Dose delivered	Number and duration of consultations
		Recruitment/reach	Number of participants, language of consultations
	Documentation sheet for mediators	Fidelity	Implementation of the module in comparison to the conceptual design (e.g., duration, contents); Feedback on implementation problems with closed and open-ended questions
Transcultural training for professionals (Module 4)			
	Recruitment monitoring	Recruitment/reach	Number of participants
	Documentation sheet for instructors	Fidelity	Implementation of the module in comparison to the conceptual design (e.g., duration, contents); Feedback from instructors on implementation problems with closed and open-ended questions
		Dose delivered	Training duration
			Subjective evaluation of implementation of the training from the instructor’s point of view
	Questionnaire for participants of the training	Recruitment/reach	Sociodemographic data of the participants

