#### Process evaluation

2.8.2.

Participants receive an anonymous questionnaire at the end of a session, which is completed on site and submitted to the instructors. The documentation and questionnaires for Modules 1, 3 and 4 are available in German. The questionnaires for participants in information events in their native language (Module 2) are available in twelve languages (see above), and are distributed according to the language of the participants. The instructors send the questionnaires, together with the completed documentation forms, by mail to the University of Lübeck, where all data is recorded electronically.

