### Data management

2.9.

A comprehensive data protection concept was developed in coordination with German pension insurance, which ensures data processing, the rights of the persons involved, as well as the technical and organizational measures for the secure and confidential collection, processing and storage of data. Researchers at the University of Lübeck only receive pseudonymized data from the insured persons and their children as part of the trend study. The generation of data within the process evaluation is anonymized. All questionnaire data is entered, checked and transferred to statistical software programs for further analysis. Data entry and data verification are performed by trained research assistants. Questionnaire data from the trend study is linked to administrative data from the insurance account using a pseudonym. Access to the data is limited to the authors and research assistants on the research team.

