## Conclusion

4.

The study described in this protocol will provide comprehensive data on which persons can be reached within the different modules of the multimodal information campaign and how the information campaign and its different modules are perceived by the participants. The results of the trend study will also provide information on whether the utilization of medical rehabilitation by children and adolescents with a migrant background could be increased over the intervention period at the intervention sites. Thus, possible changes in utilization can be related to the specific implementation of the modules of the information campaign. These data can help organizations and institutions to adapt or further develop the multimodal information campaign or specific modules for other regions in Germany or other countries.

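### Module 1: mediators' sociodemographic profile and individual attendance are collected only after the course ends, so early leavers of a nine-day training are counted but not described

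*Protocol article*

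**What the plan says.** Section 2.2.1 describes a long course: "The entire training comprises 48 teaching units of 45 min each, which are distributed over nine training days". It ends with group presentations as a final exam.

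Table 1 (section 2.3) assigns the Module 1 data as follows:

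- **Recruitment monitoring** gives a head count per training.
- **The instructors' documentation sheet** gives a head count per teaching unit, together with course duration, materials, fidelity and the instructor's assessment.
- **Questionnaire 1**, at every appointment, gives the mediators' rating of that date and their suggestions.
- **"Questionnaire 2 for mediators (after completion"** gives "Sociodemographic data of the mediators" (filed under recruitment/reach), "Data on attendance at the individual training dates" (filed under dose delivered), and the evaluation of the whole course with suggestions.

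Section 2.8.2 adds: "Participants receive an anonymous questionnaire at the end of a session, which is completed on site and submitted to the instructors". Section 2.9 states: "The generation of data within the process evaluation is anonymized". The article mentions no code that links forms from the same person.

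The Conclusion (section 4) says that the study will give "comprehensive data on which persons can be reached within the different modules" of the campaign.

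**The concern.** An attendance item answered only by people still present at the end is selected on the quantity it measures. The same selection applies to the description of who was reached, because someone who left on day three never fills in the form that asks about age, origin or education.

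This matters more for Module 1 than for the other modules. Information events last about two hours and the professional training is a one-day course, so a form at the end reaches nearly everyone there. Module 1 runs over nine days and is the module most exposed to attrition.

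At stake is a comparison that an organisation adapting the campaign would want: whether those who start the training differ from those who finish it. As Table 1 stands, that comparison cannot be made for sociodemographic characteristics.

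**Working it through.** The plan states no figure to reproduce, because section 2.6.2 makes no sample size calculation for the process evaluation. The check is a reading of Table 1, followed by an illustration with assumed rates.

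**Step 1: which sources cover an early leaver?**

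| Item | Source in Table 1 | Covers early leavers? |
|---|---|---|
| Number reached | Recruitment monitoring; instructors' sheet per unit | Yes, as a count |
| Course delivered (duration, materials) | Instructors' sheet | Yes, does not depend on finishing |
| Rating of single dates | Questionnaire 1 | Yes, for dates attended |
| Sociodemographic profile | Questionnaire 2 | No |
| Individual attendance | Questionnaire 2 | No |
| Rating of the whole course | Questionnaire 2 | No, and only finishers could give it |

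The Module 2 documentation sheet also records the sociodemographics of the mediator holding an event, but only for mediators who go on to hold events. It does not fill the gap.

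*After completion* may mean that the person has completed the course or that the course has ended. Either way, someone no longer attending does not fill in the form.

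**Step 2: how many people could this be?** The document gives no drop-out rate *d*, so I take 10%, 20% and 30%. Section 2.6.2 speaks of 120 to be recruited and section 2.2.1 of at least 120 to be trained, so I show both readings.

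- 120 start: leavers = 120 × *d* = 12, 24, 36.
- 120 finish: starters = 120 / (1 − *d*) = 134, 150, 172 (rounded up), so leavers = 14, 30, 52.

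**Step 3: how far could Questionnaire 2 attendance differ from all-starter attendance?** Assume that finishers attend 95% of units and leavers 25% to 50%, with 120 starters. All-starter mean = (1 − *d*) × 0.95 + *d* × (0.25 to 0.50).

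| *d* (assumed) | Finishers / leavers | Questionnaire 2 mean | All-starter mean | Gap (points) |
|---|---|---|---|---|
| 10% | 108 / 12 | 95% | 88.0–90.5% | 4.5–7 |
| 20% | 96 / 24 | 95% | 81–86% | 9–14 |
| 30% | 84 / 36 | 95% | 74–81.5% | 13.5–21 |

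**Step 4: is the all-starter mean lost?** No. It equals the sum of the unit head counts divided by (starters × 48). For *d* = 20% with leavers attending 50%, the head counts sum to 96 × 0.95 × 48 + 24 × 0.50 × 48 = 4377.6 + 576 = 4953.6. The denominator is 120 × 48 = 5760, and 4953.6 / 5760 = 86%, the value in the table. This works only if the denominator counts starters. With the 96 finishers instead, the result is 4953.6 / 4608 = 107.5%, which is impossible. Table 1 does not say whether its count per training means starters or finishers. If it means finishers, the largest unit head count of each course gives a lower bound for starters.

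The mean is therefore recoverable. The profile of leavers and their individual attendance patterns are not.

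**The case against.** A reader might infer that drop-outs disappear from the evaluation altogether, and that reach and dose in Module 1 describe finishers only. Table 1 does not support that. Attrition shows in the falling head counts, delivery is documented by the instructors, and people who later leave have already rated the dates they attended. Nor does any passage say that the analysts will rely on Questionnaire 2 for attendance and ignore the head counts, so it cannot be said that attendance will be reported too high.

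A reader might also infer that the overall evaluation will look too favourable, or that particular communities will be the ones missing. The document holds no evidence for either. A judgement on the whole course can come only from those who experienced it, and describing the mediators who were actually trained is a legitimate aim.

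Two further points deserve weight. The article is condensed, so the full protocol may provide an attendance register or a form code. And a code that links forms over nine days in small course groups raises a re-identification risk and touches the anonymity commitment in sections 2.8.2 and 2.9.

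These arguments narrow the point but do not remove it. Table 1 is not silent on the two items: it assigns both, explicitly, to the form given after completion.

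**Conclusion.** The point holds in a limited form. As Table 1 describes it, the sociodemographic profile and the individual attendance of mediators who leave the training early are not captured. Only head counts per training and per unit, and the per-appointment ratings, cover them. That falls short of the aim in the Conclusion to show which persons each module can reach.

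The number affected is unknown. At assumed drop-out of 10% to 30% it would be 12 to 36 people if 120 start, or 14 to 52 if 120 finish. The attendance gaps of 4.5 to 21 points rest entirely on assumed rates and arise only if Questionnaire 2 is read as describing all starters.

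Process data are presented descriptively (section 2.10), and the primary outcome, the proportion of rehabilitants with a migrant background, does not use them. This is a cheap improvement and no threat to the main result.

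**What to change.** 1. Collect the sociodemographic block anonymously on the first training day. Keep it in Questionnaire 2 as well if an aggregate comparison of starters with finishers is wanted; no linkage is needed for that.
2. Report Module 1 reach for all starters, and state that the count per training means starters.
3. Compute all-starter mean attendance as the sum of the instructors' unit head counts divided by (starters × units). Label attendance from Questionnaire 2 as finishers only.
4. For courses already held, report profile and individual attendance as finishers only.
5. Optionally, add a self-generated code so that individual attendance can be followed, but only if the data protection concept agreed with the insurer allows it.

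The cost is one short extra form on day one, and Module 1 data in two formats for earlier and later courses. The code, if used, also needs a data protection check.

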### Inclusion criteria

2.4.

#### Trend study

2.4.1.

The sample for the repeated cross-sectional survey of the trend study consists of all insured persons with the Federal German Pension Insurance, German Pension Insurance Berlin-Brandenburg, and German Pension Insurance North residing in Berlin or Hamburg whose child received medical rehabilitation through the German Pension Insurance in 2019, 2020, 2021, or 2022 and were aged from 0 to 17 years at the time of utilization. These three providers collectively account for the majority of the insured population in the two model regions, making it possible to include nearly all eligible families in the sample.

#### Processes evaluation

2.4.2.

As part of the process evaluation, all participants and instructors of the four campaign modules are asked to complete the questionnaires at the end of the modules or sessions.

### Outcomes and other measures

2.5.

#### Trend study

2.5.1.

The primary outcome of the trend study on the utilization of rehabilitation is the proportion of children and adolescents with a migrant background among those undergoing rehabilitation who reside in Berlin or Hamburg. The migrant background is assessed in this study in accordance with the minimum indicator set for recording migration status (29).

We determine an individual as having a migrant background if they immigrated from another country and have at least one parent who was not born in Germany, or have two parents who immigrated and/or do not have German nationality.

This definition allows a differentiation between children with unilateral and bilateral migrant backgrounds (30). The information on the country of birth and nationality of the parents and the child required to map the migrant background is assessed through a questionnaire, and combined with data from the insured person’s account. The primary language, residence status, and duration of residence of the child and the child’s parents are also assessed.

In order to provide a description of the samples and to describe differences between children and adolescents with and without a migrant background in the samples, the health-related quality of life of the children and adolescents [KIDSCREEN-27 (31)], sociodemographic and socioeconomic information on the children and the parental home (32), perceived social support (33) and satisfaction with the rehabilitation service received will be collected through questionnaires as part of the trend study. The questionnaire data is supplemented by administrative data on medical rehabilitation (e.g., duration, and discharge diagnosis according to ICD-10) from parents’ insurance accounts. The data collected in the trend study is shown in Table 2.

**Table 2 tab2:** Data collected as part of the trend study.

Data	Source^2^	Sample 2020	Sample 2021	Sample 2022	Sample 2023
Migration history (34)		x	x	x	x
Nationality^1^	Questionnaire for parents/administrative data	x	x	x	x
Country of birth^1^	Questionnaire for parents	x	x	x	x
Primary language^1^	Questionnaire for parents	x	x	x	x
Duration of stay^1^	Questionnaire for parents	x	x	x	x
Residence status^1^	Questionnaire for parents	x	x	x	x
Socioeconomic status (31)	Questionnaire for parents	x	x	x	x
Social support (32)	Questionnaire for parents	x	x	x	x
Health-related quality of life (KIDSCREEN-27) (30)		x	x	x	x
Physical wellbeing	Questionnaire for parents/child	x	x	x	x
Psychological wellbeing	Questionnaire for parents/child	x	x	x	x
Parent relations and autonomy	Questionnaire for parents/child	x	x	x	x
Social support and peers	Questionnaire for parents/child	x	x	x	x
School	Questionnaire for parents/child	x	x	x	x
Satisfaction with rehabilitation	Questionnaire for parents/child	x	x	x	x
Start of rehabilitation	Administrative data	x	x	x	x
End of rehabilitation	Administrative data	x	x	x	x
Approval diagnosis (ICD-10)	Administrative data	x	x	x	x
Discharge diagnosis (ICD-10)	Administrative data	x	x	x	x

^1^Data is collected for the child and both birth parents. ^2^The parent questionnaire is sent to the parent who requested the child’s medical rehabilitation, and includes a section for information about the other parent; Administrative data is extracted from the insurance account of the parent who applied for medical rehabilitation.

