### Medical rehabilitation for children and adolescents

1.3.

In general, children with chronic diseases in Germany are treated on an outpatient basis close to home by pediatricians or family doctors, in collaboration with other therapists (e.g., physiotherapists, child and adolescent psychotherapists). Outpatient treatment, however, may be not sufficient for some individuals. In these cases, the German social insurance system offers medical rehabilitation for children and adolescents (MRCA) (13). The legal basis for this is § 15a SGB VI. MRCA is intended to counteract the consequences of chronic illness, to enable schooling and vocational training without restrictions, and, in the long term, to prevent endangerment to, or the restriction of, gainful employment. In Germany, statutory health insurance and German Pension Insurance (GPI) are in principle equally responsible for medical rehabilitation. Despite this, the primary provider of MRCA services is the GPI. Every year, more than 32,000 requests for medical rehabilitation for children and adolescents are submitted to the German Pension Insurance. In Germany, medical rehabilitation for children and adolescents takes place almost exclusively in inpatient rehabilitation clinics. The most common reasons for using MRCA in 2018 were mental and behavioral disorders, followed by bronchial asthma, obesity and skin diseases such as neurodermatitis (14). Reliable data on the utilization of medical rehabilitation by children and adolescents with MB is not currently available, as the GPI administratively only records the nationality of rehabilitants. In terms of nationality, however, there is a clear underrepresentation of children and adolescents of non-German nationality (14). A recent study with adults shows that in addition to underutilization among persons without German nationality, underutilization by persons with a migration history can also be assumed (15). Possible reasons for this are utilization barriers such as insufficient language skills, a different understanding of illness, or insufficient knowledge of the German health care system (16).

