**Figure 1 fig1:**
[figure not shown]
Proportion of the population with a migrant background in the 0 to 17 age group by federal state in Germany in 2019; Own representation based on data from the Federal Statistical Office (3).

The implementation is accompanied by a process evaluation (20). The effect of the intervention (i.e., increase in utilization of MRCA by children and adolescents with a migrant background) will be tested with a repeated cross-sectional survey (trend study) with four measurement points. The information campaign will be implemented by the Ethno-Medical Center. The process evaluation and the trend study are both implemented by the Institute of Social Medicine and Epidemiology of the University of Lübeck (UoL). The implementation of the information campaign, the implementation of the trend study and the process evaluation are accompanied by an advisory board, which consists of responsible persons from the GPI BB and GPI North sponsors as well as migration experts and specialists from the fields of pediatric and adolescent medicine and medical rehabilitation. The advisory board meets every six months and uses its expertise to address problems that arise during the implementation. The project started in April 2019, and once the campaign module design and materials development were completed, the campaign modules began implementation in September 2020. Implementation of the campaign modules and process evaluation will continue to the end of 2022. The final survey of the trend study will take place at the end of 2023.

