#### Trend study

2.7.1.

In the fourth quarter of 2020 to 2023, the German Pension Insurance identifies, based on administrative data, all insured persons residing in Berlin or Hamburg who have a child who received medical rehabilitation from the German Pension Insurance in the previous year (i.e., 2019, 2020, 2021, and 2022) and who was 17 years old or younger at the time of rehabilitation. These insured persons form the sample of the trend study.

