### Statistical methods

2.10.

Changes in the proportion of individuals with a migrant background in the samples will be analyzed using a Cochrane-Armitage test for trend (36). We will use unpaired t-tests for metric data, a Mann–Whitney U-test for ordinal data, and chi-square test for nominal data to describe differences between rehabilitants with and without migrant backgrounds in the samples. We will not perform interim analyses and did not specify a stopping rule. The results of statistical tests will be considered significant if the two-sided value of p of the test is less than 0.05. Process evaluation data is descriptively presented. A current version of Stata (StataCorp, College Station, Texas, USA) will be used to perform the analyses.

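### The tested outcome is the migrant share of rehabilitants, a measure of relative representation, but the article draws its conclusion about whether migrant children's utilisation increased

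*Protocol article*

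**What the plan says.** **Outcome and test.** Section 2.5.1 says that the primary outcome "is the proportion of children and adolescents with a migrant background among those undergoing rehabilitation who reside in Berlin or Hamburg". Section 2.10 gives its analysis: "Changes in the proportion of individuals with a migrant background in the samples will be analyzed using a Cochrane-Armitage test for trend". Results are "considered significant if the two-sided value of p of the test is less than 0.05". The sample size in section 2.6.1 is built on the same share, assumed to go from 10 to 11, 13 and 16%.

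**Who is sampled.** Only users of rehabilitation are in the frame: insured persons "whose child received medical rehabilitation through the German Pension Insurance in 2019, 2020, 2021, or 2022" (section 2.4.1). Each year the pension insurance identifies "all insured persons residing in Berlin or Hamburg who have a child who received medical rehabilitation" (section 2.7.1), so the yearly total is known to the carriers. Migrant background is not known to them, because "the GPI administratively only records the nationality of rehabilitants" (section 1.3); it comes from the questionnaire.

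**What is to be concluded.** Section 2.1 describes the effect of the intervention as an "increase in utilization of MRCA by children and adolescents with a migrant background". Section 1.4 states the aim in terms of access and utilisation among migrant children. Section 4 says that the trend study will show "whether the utilization of medical rehabilitation by children and adolescents with a migrant background could be increased over the intervention period". The article describes no count of migrant users to go with the share.

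**The concern.** Write M for rehabilitants with a migrant background and N for those without. The outcome is M/(M+N). The conclusion concerns M, or M relative to the migrant children who could have used the service. The two agree only if N stays roughly constant.

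Two errors are possible when the plan is followed as written. If N falls while M is flat or falls less steeply, a significant upward trend would be reported as increased utilisation although no more migrant children were treated. If M and N grow together, the share does not move and a real increase in M goes unseen. This is not a detail left to an analysis plan: the article itself fixes the outcome, the test and the conclusion, and they do not match.

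**Working it through.** **Inputs from the article.** Shares of 10, 11, 13 and 16%; 432 persons per year; 1,200 rehabilitants per year, 40% participation and 84% power (all section 2.6.1); two-sided 0.05 (section 2.10).

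**Step 1: reproduce the plan's figures.** Cochran-Armitage test, scores x = 0, 1, 2, 3 (mean 1.5), equal n per year, mean share 0.125, no continuity correction.
- Mean of the statistic: n × Σ(x − 1.5)p = n × 0.10.
- Null variance: n × 0.125 × 0.875 × 5 = n × 0.546875.
- Alternative variance: n × Σ(x − 1.5)²p(1 − p) = n × 0.55765.
- Power = Φ[(mean − 1.96 × √null variance) / √alternative variance].

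For n = 432: (43.2 − 1.96 × √236.25) / √240.90 = 0.84, so power is 80.0%. For n = 0.40 × 1,200 = 480: (48.0 − 1.96 × √262.5) / √267.67 = 0.99, so power is 84.0%. Both figures reproduce, and simulation agrees. The sample-size arithmetic is sound for the share.

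**Step 2: the same share from two different situations.** In the first year M = 0.10 × 1,200 = 120 and N = 1,080.
- If N stays at 1,080, a share of 16% needs M = 1,080 × 0.16/0.84 ≈ 206, which is 86 more migrant children.
- If M stays at 120, a share of 16% needs a total of 120/0.16 = 750, so N = 630. That is a fall of 450/1,080 ≈ 42% with no additional migrant child.

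The share is identical in the two cases.

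**Step 3: how often the planned test would be significant with M constant.** *Assumption:* M = 120 every year, and N falls linearly to the stated level in year 4. Respondents are 40% of each year's total, and the two-sided 0.05 trend test is simulated 200,000 times.

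| Fall in N by year 4 | Share in year 4 | Significant trend |
|---|---|---|
| 10% (N = 972) | 120/1,092 = 11.0% | about 8% |
| 15% (N = 918) | 120/1,038 = 11.6% | about 12% |
| 20% (N = 864) | 120/984 = 12.2% | about 19% |
| 30% (N = 756) | 120/876 = 13.7% | about 41% |

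The path N = 1,080, 971, 803, 630 (not linear; falls of 10, 26 and 42%) gives exactly the planned 10, 11, 13 and 16%. The trend is then significant in about 73% of runs. This is below 84% only because the yearly samples shrink from 480 to 300.

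**Step 4: the opposite case.** If both groups grow linearly by 60%, M goes from 120 to 192 and N from 1,080 to 1,728. The share is 192/1,920 = 10% throughout, and the test is significant in about 5% of runs, its nominal level. With the same rise in M and N unchanged, it would be significant in about 72%.

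**The case against.** The strongest reply is that the share is a deliberate and defensible choice. The abstract and the discussion speak of reducing disparities and inequality, and section 1.3 frames the problem as underrepresentation. A share among users measures that directly. In the 30% case the ratio of migrant to non-migrant users goes from 120/1,080 to 120/756, a 1.43-fold rise. That is a genuine narrowing, and it is also what would be seen if the campaign held migrant use up during a general decline. Outcome, sample size and test agree with one another. All of this stands, and it is why the share should remain the primary outcome.

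It is also fair that nothing in the article suggests that non-migrant use will fall by 30 or 42% while migrant use stays flat. It is equally fair that the modules are aimed at migrant communities, so a proportional rise in both groups is not the expected result. The scenarios show what the test cannot distinguish; they do not forecast what will happen. With small falls in N the harm is small.

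A reader might infer more than the documents support:
- *That any change in overall volume distorts the share.* It does not: if both groups change by the same factor, M/(M+N) is unchanged.
- *That growth of the migrant child population raises the share with nobody extra treated.* At constant use per child, that growth means more migrant children are treated. It would raise the count as well as the share, so it is a different problem from the one here.
- *That the share is invalid as an outcome.* It is valid for relative representation.

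None of this answers the wording of sections 1.4, 2.1 and 4, which speak of utilisation increasing and not of a gap narrowing.

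**Conclusion.** The mismatch holds. The outcome and its only test concern the migrant share of rehabilitants, while the aim, effect and conclusion concern utilisation by migrant children. On its own, the share supports a statement on relative representation and not one on increased utilisation.

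The size depends on how non-migrant use moves, for which the article gives no figure beyond 1,200 rehabilitants a year. With M constant at 120 and 40% participation, the chance of a significant trend runs from about 8% (N down 10%) to about 41% (N down 30%), and to about 73% on the path that mimics the planned effect. These figures assume binomial sampling and equal participation in the two groups.

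**What to change.** 1. Keep the share as the primary outcome and the trend test as its analysis. State that it measures relative representation, that is, disparity.
2. For each of the four survey years, report the carriers' total number of rehabilitants in the frame and the estimated counts: migrant = share × total, non-migrant = (1 − share) × total. Give confidence intervals and a caveat on non-response.
3. Conclude that utilisation by migrant children increased only if the estimated migrant count also rises. Otherwise, word the statements in sections 2.1 and 4 as a change in the share of rehabilitants.
4. Treat population-based rates as optional. They make sense only if the official definition of migrant background (own or family migration history, section 1.1) can be matched to the rule in section 2.5.1, and the resident population to those insured with the three carriers in section 2.4.1.

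**Cost.** A little extra analysis and no new data collection, since the totals follow from drawing the frame. The counts carry the same non-response uncertainty as the share and are not precise. At a share of 10% with 480 respondents, the 95% interval is about 1,200 × 1.96 × √(0.10 × 0.90/480) ≈ ±32 around 120 (simple binomial, no finite-population correction). The count also cannot separate better access from growth in the migrant child population, so the conclusion should say so.
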